**Methods and analysis:**

This multicentre, randomised controlled parallel-group trial is planned to be conducted within two specialised orthopaedic outpatient rehabilitation units in the southeast healthcare region of Sweden. Eligible patients (40–85 years, awaiting unilateral TKR) are randomised 1:1, stratified by age (≤67, >67 years), to either 8 weeks of prehabilitation—comprising two times per week supervised exercise therapy (strength, range of motion and balance) and education—in addition to standard care, or to standard care alone. Standard care consists of self-care, a single standardised preoperative education session and standardised postoperative rehabilitation. Assessments are conducted at baseline, post-intervention, 1 week pre-surgery and 6, 12 and 52 weeks post-surgery. A total of 110 patients will be recruited to the trial. Primary outcomes are joint awareness (Forgotten Joint Score-12) and patient enablement (modified Patient Enablement Instrument-2). Secondary outcomes are patient satisfaction (5-category Likert scale), the Knee injury and Osteoarthritis Outcome Score, the EuroQol 5 Dimension 3 Level questionnaire, the International Physical Activity Questionnaire—short form, objective function and accelerometer-based physical activity. Analyses will follow intention-to-treat and per-protocol principles. Between-group and within-group differences will be tested using t-tests or non-parametric equivalents, and linear mixed models or generalised linear models. Multiple linear regression and logistic regression will be used to analyse predictor variables for the primary outcomes. Sensitivity analyses will be performed to quantify the magnitude of missing data from patients lost to follow-up.

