### Sample size

To detect a difference in the MIC of 17.7 points (effect size 0.61) and the MCID of 13.7 points between the SC+P and SC groups in the FJS-12^16^ from baseline to the 52-week follow-up, and assuming a 0.6 proportion of total scores >21 points for the Mod-PEI-2 in the SC+P group versus 0.3 in the SC group at the 6-week follow-up, a total of 110 patients is targeted for inclusion across the two groups (80% power, 5% α-level, with an estimated 20% dropout included).

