### Analysis plan

All analyses will be performed using IBM SPSS Statistics software, V.29, applying intention-to-treat and per-protocol approaches with an α-level of 0.05. Demographic data will be presented as mean or median with SD or IQR for quantitative variables, and as frequencies and percentages for categorical variables.

Depending on measurement scale and distribution, differences between groups at baseline and for primary and secondary outcomes at each follow-up assessment will be analysed using independent samples t-tests or non-parametric equivalent tests. Longitudinal changes within groups from baseline to follow-up time points will be analysed using linear mixed models or generalised linear models, with baseline measurements included as covariates. Multiple linear regression and logistic regression will be used to analyse predictor variables for the primary outcomes (FJS-12 and Mod-PEI-2). Furthermore, analyses of primary and secondary outcomes will be adjusted, if necessary, for differences in intervention delivery and adherence, duration of participation, surgical procedures and postoperative physiotherapy care.

Multiple analyses will be performed using α-level adjustment methods, such as the Bonferroni method. In the intention-to-treat analysis, a sensitivity analysis will be performed to quantify the magnitude of missing data from patients lost to follow-up. Appropriate statistical methods will be used to account for missing data in the analysis, depending on the characteristics of the missing data. If there is extensive missing data, a second table of baseline characteristics will be presented only for patients included in the final analysis. The proportion of missing outcomes per group, characteristics of patients with missing data and possible reasons for missing outcome data will be presented.

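### Bonferroni is the only multiplicity method named; if it is applied across the two primary outcomes, Holm's step-down test would keep the same 5% family-wise error and gain about 5 to 6 points of power per outcome

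*Protocol article*

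**What the plan says.** The abstract gives two primary outcomes: "Primary outcomes are joint awareness (Forgotten Joint Score-12) and patient enablement (modified Patient Enablement Instrument-2"). Table 3 and the Sample size section place their main time points at 52 weeks (FJS-12) and 6 weeks (Mod-PEI-2) after surgery.

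The Analysis plan section sets the general level, "applying intention-to-treat and per-protocol approaches with an α-level of 0.05". On multiplicity it has one sentence: "Multiple analyses will be performed using α-level adjustment methods, such as the Bonferroni method". It does not say which tests form the family, or whether the two primary outcomes are adjusted against each other.

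The Sample size section uses "80% power, 5% α-level, with an estimated 20% dropout included", with no division of alpha between the outcomes.

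**The concern.** Single-step Bonferroni on two outcomes tests each at 2.5%, even after the other has already succeeded. Holm tests the smaller p-value at 2.5% and, if that passes, the larger at 5%. Both procedures hold the family-wise error at 5% under any dependence between the tests, and Holm never rejects less. The one method the plan names is therefore dominated for this purpose.

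The power at stake matters because the sample size leaves no reserve for an alpha split, and the stated aim covers both joint awareness and enablement. This is a separate question from which alpha the sample size should have used: with a larger trial or a restated power, Holm would still be at least as powerful on the same data.

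**Working it through.** **Inputs (Sample size section, except as noted).** FJS-12: "To detect a difference in the MIC of 17.7 points (effect size 0.61"), which implies an SD of 17.7/0.61 = 29.0. Mod-PEI-2: "assuming a 0.6 proportion of total scores >21 points for the Mod-PEI-2 in the SC+P group versus 0.3 in the SC group". Size: "a total of 110 patients is targeted for inclusion across the two groups". Allocation is 1:1 (Randomisation section). After 20% dropout, 110 × 0.8 = 88, or 44 evaluable per arm. Assumptions of this check: two-sided tests (sidedness is not stated), and a family of exactly the two primary outcomes.

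**1. Reproducing 110.**
- FJS-12, normal approximation: n = 2(1.960 + 0.842)²/0.61² = 42.2, so 43 per arm. The t-test calculation gives 43.2, so 44 per arm, and 88/0.8 = 110.
- Mod-PEI-2, two proportions without continuity correction: 42 per arm, and 84/0.8 = 105.
- The figure therefore reproduces with an unadjusted 5% for each outcome. The section also names "the MCID of 13.7 points between the SC+P and SC groups in the FJS-12". At SD 29.0 that is an effect size of 0.47 and needs about 72 per arm, or 144/0.8 = 180 in total, so 110 corresponds to the 17.7-point difference only.

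**2. Power per outcome at 44 per arm.**
- FJS-12: noncentrality 0.61 × √(44/2) = 2.86. The t-test has 80.8% power at 5% and 71.8% at 2.5%.
- Mod-PEI-2: power = Φ[(0.3√44 − z√(2 × 0.45 × 0.55))/√(0.24 + 0.21)]. With z = 1.960 this is Φ(0.911) = 81.9%. With z = 2.241 it is Φ(0.616) = 73.1%.

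**3. Holm, by hand, for independent tests.** An outcome is rejected if its own p is at most 0.025, or if it lies between 0.025 and 0.05 and the other p is at most 0.025.
- FJS-12: 0.718 + (0.808 − 0.718) × 0.731 = 78.4%.
- Mod-PEI-2: 0.731 + (0.819 − 0.731) × 0.718 = 79.4%.

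**4. Correlated test statistics.** Two million simulated pairs of normal test statistics, 44 per arm, 17.7-point effect. On the normal scale FJS-12 power runs about one point above the t-test figure, so the gains are the useful columns.

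| Correlation | Gain per outcome (points) | Both, Bonferroni | Both, Holm | Gain for both (points) | At least one, either method |
|---|---|---|---|---|---|
| 0 | 6.2 | 53.9% | 66.2% | 12.3 | 93.0% |
| 0.3 | 5.6 | 57.3% | 68.4% | 11.1 | 89.5% |
| 0.5 | 5.1 | 59.9% | 70.2% | 10.2 | 86.8% |
| 0.8 | 4.3 | 65.1% | 73.6% | 8.5 | 81.8% |

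Adding the gain at correlation 0.5 to the step 2 figures gives 71.8 + 5.1 = 76.9% and 73.1 + 5.1 = 78.2%. Over correlations of 0 to 0.5, Holm therefore gives about 77–79% per outcome. With FJS-12 matched to its t-test power, the figures for both are about one point lower (53.1% to 65.4% at correlation 0), with almost the same gain.

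**5. Type I error.** If both null hypotheses are true, either procedure makes an error only when the smaller p is at most 0.025, which has probability at most 5%. If one is true, Holm can reject it only when its p is at most 0.05. Simulated family-wise error with both nulls true was identical for the two methods: 4.95% at correlation 0 and 4.7% at 0.5.

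**6. Sensitivity.**
- No dropout (55 per arm): the gain is about 4–5 points per outcome and 8–10 for both, at correlations of 0 to 0.5.
- FJS-12 difference of 13.7 points, 44 per arm: the gain is uneven, about 8 points for FJS-12, 3–4 for Mod-PEI-2 and 11–12 for both.

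**The case against.** The strongest objection concerns the text. A reader might infer that the plan commits to single-step Bonferroni and that the trial is giving away this power. The document does not support that. Bonferroni is introduced by 'such as', as one example of a class to which Holm also belongs, and an analysis plan that is not shown may settle the choice. This stands, and the point is conditional for that reason.

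A reader might also infer that the two primary outcomes form the family. The document does not say so. The sentence follows text on baseline comparisons, secondary outcomes at every follow-up, within-group changes and predictor models. With no alpha split in the sample size, one can read the plan as keeping 5% for each primary outcome and adjusting only the rest. On that reading Bonferroni costs the primary outcomes nothing. This also stands: the figures hold only for a family of exactly these two.

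Third, no rule requires both outcomes to succeed. If both were required, each could be tested at 5% without adjustment. If either suffices, Holm does not change the chance of at least one success. That is correct. The gain lies in the separate claim for each outcome and in the chance of supporting both when each is claimed on its own merits.

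Finally, Bonferroni does offer something in return: simple simultaneous confidence intervals. Holm-adjusted p-values can also disagree with ordinary 95% intervals. With p-values of 0.03 and 0.04, Holm rejects neither, yet both intervals exclude no effect. This is a real but small drawback, met by labelling the intervals.

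The objections do not remove the point that the only method named is dominated by one just as easy to apply.

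**Conclusion.** The point holds in conditional form. If Bonferroni is applied across FJS-12 at 52 weeks and Mod-PEI-2 at 6 weeks, power is about 72–73% for each. Holm on the same p-values would give about 77–79% at the same 5% family-wise error. The gain is 5–6 points per outcome and 10–12 for showing both at correlations of 0 to 0.5, falling to about 4 and 9 at 0.8. Power for at least one is unchanged.

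These sizes rest on 44 evaluable patients per arm, the 17.7-point effect, 0.6 versus 0.3, two-sided tests and a family of two. That Holm is never worse for rejection depends on none of the effect-size, sample-size or correlation assumptions. Naming Bonferroni as an example is not an error in itself, because the method is valid.

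**What to change.** For the two primary outcomes, replace the open-ended Bonferroni example with a sentence such as: *FJS-12 at 52 weeks and Mod-PEI-2 at 6 weeks will be tested by the Holm step-down procedure at a two-sided family-wise 5%: the smaller p-value is tested at 2.5% and, if significant, the other at 5%.* Report Holm-adjusted p-values together with 95% confidence intervals labelled as unadjusted for multiplicity.

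The cost is one sentence, with no new data and no change for patients. The downside is that simultaneous confidence intervals matching the test are less simple than under Bonferroni. The article expects data collection to finish at the end of 2027 and lists an unblinded statistician among its limitations, so the procedure is best fixed before outcome data are examined.

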### Patient and public involvement

Patients with knee OA were involved in the early planning stage of this trial by providing their perspectives on the time frame from referral in primary care to consultation with the orthopaedic surgeon and subsequent surgery. This input was used to inform the planning of the intervention. After completion, the RCT will be followed by a qualitative interview study with participants from the intervention group to explore the feasibility of implementing the intervention in clinical practice.

## Ethics and dissemination

The trial has received ethical approval from the Swedish Ethical Review Authority (reg. no. 2023-05120-01) and is pre-registered at ClinicalTrials.gov (trial no. NCT06290336). The trial complies with the Declaration of Helsinki. It is funded by the Medical Research Council of Southeast Sweden, which has not been and will not be involved in planning, conducting, analysing or presenting the results. Signed informed consent is obtained from all patients before participation in the trial (online supplemental file 1).

Dissemination of aggregated trial results to relevant professional and patient interest groups will be conducted through conference presentations, meetings and submission for publication in a peer-reviewed journal. The findings may influence future clinical guidelines and care pathways for patients undergoing TKR.

### Trial status, anticipated time frame and changes to the protocol

All patients booked for an initial assessment by an orthopaedic surgeon receive letters of invitation together with written trial information 1–2 months prior to the scheduled visit. The letters and trial information began to be sent out in December 2023, and the first eligible patient was recruited on 26 February 2024. Recruitment is expected to continue throughout 2026, and subsequent data collection is anticipated to be completed by the end of 2027.

Patient satisfaction with the results 52 weeks after surgery was changed from a primary to a secondary outcome after the initiation of the trial, as satisfaction is closely linked to and captured by the current primary outcome measure, FJS-12.^15 16^ Furthermore, after recruitment of the first 22 patients, measurement of objective physical activity using the activPAL accelerometer was added to the secondary outcomes to supplement the existing physical activity PROMs.

## Discussion

### Strengths and limitations

Strengths of this trial include the following: (1) concealed, stratified randomisation to reduce the risk of allocation bias; (2) supervised exercise therapy, allowing easy monitoring of exercise technique, dosage and progression; (3) blinded assessors of objective outcomes to reduce the risk of detection bias; (4) multicentre design to increase external validity; (5) individualisation of total exercise number and variations, enabling tailored exercises and promoting person-centred care; (6) intervention delivered in a group format, offering peer support; (7) combination of exercise therapy and patient education according to recommendations, improving functional performance and creating realistic expectations among patients awaiting TKR; and (8) opportunity to ask individual questions and engage in discussion with physiotherapists experienced in preoperative and postoperative rehabilitation of TKR.

Limitations of this trial include the following: (1) waiting time to surgery will differ between patients, resulting in variable total exposure time and challenges for statistical analysis; (2) the combined intervention design does not allow differentiation between the effects of exercise therapy and patient education; (3) on-site intervention delivery at a set time in the afternoon may exclude patients with long travel distances and make participation difficult for working-age patients or those with other commitments; (4) individualisation of exercise therapy and patient education may limit comparability with other studies and generalisability of results, although individualisation is performed within predetermined boundaries; (5) patients’ expectations may increase as a result of the intervention, potentially raising the risk of dissatisfaction if expectations are not fulfilled; (6) satisfaction is a multifactorial concept and challenging to assess comprehensively^59 60^; and (7) the trial coordinator (primary investigator) and statistician are not blinded to group allocation.

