### Data management and patient confidentiality

All digital trial data are stored on a secure server managed by Region Östergötland. All physical trial documentation (envelopes, surveys, exercise protocols, etc) is stored in a fireproof locker accessible only to the research group. Patients are assigned a unique three-digit ID, and the key code is accessible only to the trial coordinator. Only coded data are shared among the authors in the research group.

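### The statistician is unblinded while test, adjustment and missing-data choices depend on the observed data, so they can be made knowing which arm they favour

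*Protocol article*

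**What the plan says.** Limitation 7 in the Discussion (Strengths and limitations) states that "the trial coordinator (primary investigator) and statistician are not blinded to group allocation".

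The Analysis plan leaves these choices to the data:

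- **Test.** "Depending on measurement scale and distribution, differences between groups at baseline and for primary and secondary outcomes" at each follow-up are to be analysed with "independent samples t-tests or non-parametric equivalent tests".
- **Adjustment.** "analyses of primary and secondary outcomes will be adjusted, if necessary, for differences in intervention delivery and adherence", and also for "duration of participation, surgical procedures and postoperative physiotherapy care". No criterion for necessity is given.
- **Missing data.** The method is to follow from the characteristics of the missing data.

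The same section gives "linear mixed models or generalised linear models, with baseline measurements included as covariates" for longitudinal change within groups.

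Data collection and blinding describes masking only for the physiotherapists who assess objective function. Patients know their arm but are not told the trial hypothesis until data collection ends. Data management and patient confidentiality adds that "Only coded data are shared among the authors in the research group". This refers to three-digit patient IDs whose key only the coordinator holds.

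**The concern.** Either feature alone would be less troubling. An unblinded statistician following a fixed analysis has little room to influence the result. A masked statistician choosing a test by distribution does not know whom the choice helps. Here the two are combined: whoever decides whether a distribution calls for a rank test, whether adjustment is necessary, or how to treat dropouts may already know what each option does to the prehabilitation arm.

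Both primary outcomes, the Forgotten Joint Score-12 (FJS-12) and the modified Patient Enablement Instrument-2 (Mod-PEI-2), are reported by patients who know their allocation. Assessor blinding does not reach these outcomes. Withholding the hypothesis gives them some protection, and a masked primary analysis would add to it. At stake is whether a reader can trust that the reported analysis was not steered, even unintentionally, towards one arm.

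**Working it through.** **1. Which choices really depend on the data**

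- *t-test or rank test.* Measurement scale is known in advance, so only the distribution part is open. Pooled data without arm labels can show it.
- *Mixed or generalised linear model.* This can follow from outcome type: Sample size treats FJS-12 as a score and Mod-PEI-2 as a proportion above 21. The Analysis plan also ties these models to within-group change, although the Abstract lists them together with the between-group tests. I do not count this choice.
- *Adjustment.* This is the most open choice. No trigger is stated, and every listed variable (delivery, adherence, duration, surgery, postoperative physiotherapy) becomes known only after randomisation.
- *Missing-data method.* It depends on the missing data seen, which are also to be reported by group.
- *Multiplicity.* "Multiple analyses will be performed using α-level adjustment methods, such as the Bonferroni method" names a method only as an example. It is not tied to the data, so I do not count it.

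Three choices remain, and the article says that the person analysing the data knows the allocation.

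**2. Can the effect of unblinding be given a number?**

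The plan's own size comes first. A two-sample t-test with effect size 0.61, 5% α (two-sided assumed) and 80% power needs 43.17, so 44 per arm. Then 2 × 44 = 88, and 88 / (1 − 0.20) = 110, the stated total. This point does not change it.

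Next, 8,000 simulated null trials were run per setting, with 44 per arm, a normal outcome and four balanced optional covariates. Covariate–outcome correlations were 0.2, 0.3 and 0.4. The simulation settings are assumptions, not figures from the documents.

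- Fixed t-test: 5.35%, 4.95%, 4.81%.
- Smaller p of t-test and Mann-Whitney: 6.19%, 5.91%, 5.38%. The increase is 0.84, 0.96 and 0.56 percentage points.
- Smallest p when adjusted models may also be chosen: 9.6%, 11.5%, 13.6%.
- The same, counting only results that favour prehabilitation: 4.9%, 5.8%, 7.0%, about half of the line above.

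These rates do not measure unblinding. Swapping the arm labels turns t into −t and U into n₁n₂ − U, and reverses the sign of a regression coefficient. Every two-sided p-value stays the same. An analyst who sees arms A and B and picks the smallest p reaches the same error rate. The figures describe an analysis that is not fixed, and the larger ones also rest on assumed covariates.

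**3. Is masking feasible?**

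Table 3 gives one outcome schedule for all patients. The records that reveal the arm can be separated: the prehabilitation exercise journal and the form on outside exercise for standard-care patients (both under Adherence), and injuries sustained during the intervention (Adverse events). The ID coding does not by itself hide the arm, so masking would be a new step.

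**The case against.** The strongest reply has four parts.

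*The authors disclose it, and a separate analysis plan may fix the choices.* Part of this stands. A protocol article may leave the exact test, covariate criterion and missing-data method to an analysis plan, and such a plan would shrink the risk. But the article positively states that the statistician is unblinded and that choices follow the observed data. This is a stated design choice, not an omission, and disclosing a risk does not reduce it.

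*The harm is not quantified.* This stands. A reader might infer that unblinding raises the type I error by a calculable amount. The documents do not support that: the simulated rates are unchanged by swapping labels, and the choice between t-test and rank test adds less than one percentage point.

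*Masked analysis is not the only protection left for the patient-reported outcomes.* This also stands. A reader might see the analyst as the last safeguard, but the hypothesis is withheld from patients.

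*A and B labels are a weak remedy.* Part of this stands. Labels alone do not stop selection by p-value. Strength and chair-stand results after eight weeks of supervised training could give the arms away. Adjustment for adherence cannot be done masked, because the prehabilitation journal exists in one arm only. For these reasons the choices must be fixed before any by-arm comparison, and adherence analyses must come after unmasking.

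**Conclusion.** The point holds as an avoidable and disclosed risk of bias. The article combines an unblinded statistician with choices of test, adjustment and missing-data method that depend on the data, and it describes no safeguard for the analysis. I judge the risk moderate, with open-ended adjustment the largest part and the distribution-based test choice a small one. This is a judgement; the documents do not allow a figure. It rests on the article as published and would weaken if an analysis plan not shown here fixes these choices before any by-arm comparison. Nothing in the documents suggests that the choices have been or will be misused, and the sample size of 110 is unaffected.

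**What to change.** 1. Before anyone makes a by-arm comparison, fix in writing the test, model, covariates and missing-data method for FJS-12 and Mod-PEI-2. Where the data must be inspected first, use pooled data without arm labels.
2. Give the statistician a file with arms labelled A and B that excludes the exercise journal, the exercise form used only for standard-care patients, and the intervention-injury records. The primary intention-to-treat analysis is run on this file.
3. Open the key only after that analysis is locked.
4. Run per-protocol analyses, and any analysis that uses adherence or intervention delivery, after unmasking and label them as secondary.
5. Reword limitation 7 to say that the coordinator is unblinded and the statistician is masked for the primary analysis.

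The cost is a short data-management addition and separate files, with no extra staff or visits. There is time: recruitment is expected to continue throughout 2026 and data collection to finish by the end of 2027. The downsides are that adherence and per-protocol results wait until unmasking, and that masking may be imperfect if large functional differences let the arms be guessed.
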